## Methods: participants, interventions, and outcomes

### Study setting {9}

The trial sites are located in Magdeburg (Magdeburg-Stendal University of Applied Sciences, Department of Engineering and Industrial Design (IWID), Chair of Human-Technology Interaction, [name]) and Stendal (Magdeburg-Stendal University of Applied Sciences, Department of Applied Human Sciences (AHW), Chair of Clinical Neuropsychology, [name]). Recruitment and data collection will take place at care providers and logistics companies in Germany. The expected duration of the trial is 3 years, including participant enrollment, intervention implementation, assessments, and data analysis.

### Eligibility criteria {10}

In this trial, employees from the logistics and healthcare sectors working in cooperating institutions will be recruited. For the purpose of this study, logistics occupations are defined as jobs that involve manual handling tasks such as lifting, carrying, or moving goods (e.g., warehouse workers, order pickers, and employees involved in internal transport processes). Healthcare occupations include nursing staff working in inpatient or outpatient settings whose routine duties involve manual patient handling tasks such as lifting, transferring, or repositioning patients.

Prior to study initiation at trial sites, cooperation agreements will be established only with companies in which routine work tasks involve high exposure to manual lifting and carrying loads. High-risk exposure is defined as performing more than 10 lifting or carrying tasks per working day or handling loads exceeding 10 kg per lifting or carrying task.

To ensure that these criteria are met, participating companies will be visited in advance, and relevant departments and job roles will be identified in collaboration with company management and supervisory staff. Only employees working in these predefined departments and roles will be invited to participate in the study.

Eligible participants must have sufficient proficiency in German or English to understand the study information, complete questionnaires, and participate in interviews, as all study instruments are only available and validated in these languages. Exclusion criteria include inability to understand study procedures or to complete required assessments, as well as inability or unwillingness to comply with study procedures over the 3-month intervention period.

The inclusion and exclusion criteria are listed in Table 1. Eligible employees will be recruited and randomized.

**Table 1 Tab1:** Criteria for inclusion and exclusion

Inclusion criteria	Exclusion criteria
• Workers from the logistics or healthcare sectors whose regular occupational tasks include recurring manual lifting or carrying activities • High-risk exposure to lifting and carrying loads, defined as performing more than 10 lifting or carrying tasks per working day or handling loads exceeding 10 kg per lifting or carrying task • Age over 18 years • Sufficient proficiency in German or English to understand study procedures and complete questionnaires and interviews	• Acute viral/bacterial infections and infectious diseases • Orthopaedic, rheumatological, cardiovascular, or psychiatric conditions that prevent the use of passive exoskeletons • Inability to understand study procedures or to complete questionnaires and required assessments • Inability or unwillingness to comply with study procedures over the 3-month intervention period • Pregnancy • Other conditions that lead to severe physical or psychological limitations

### Who will take informed consent? {26a}

Informed consent will be obtained by trained research staff members. During a personal conversation, the research staff members will provide detailed explanations about the study objectives, purpose, procedures, harms, and participants’ rights. At this stage, employees will receive written information as well as detailed informed consent. After an appropriate period for consideration, participants will have the opportunity to ask questions, verification of inclusion and exclusion criteria will be conducted, and written consent will be obtained.

### Additional consent provisions for collection and use of participant data and biological specimens {26b}

N/A. No biological specimens were collected as part of this trial.

## Interventions

### Explanation for the choice of comparators {6b}

The comparator in this trial is standard care without the use of a back-support exoskeleton. This choice reflects the current standard practice in logistics and nursing professions, where no assistive exoskeletal devices are typically used. By comparing the use of a passive back-support exoskeleton to usual practice, the study aims to evaluate the added value of the intervention under real-world conditions. This comparison allows for a clear assessment of the effectiveness, usability, and safety of the device relative to the current occupational norms.

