**Methods:**

ELSA LogiCare is a multicenter, parallel-designed, randomized controlled trial. Participants will be randomly assigned in a 2:1 ratio to either an intervention group or a control group. The intervention group will be randomly assigned (1:1) to use one of two passive back-support exoskeleton models for 3 months, while the control group works unassisted as usual. We aim to recruit a total sample size of 120 participants, resulting in approximately 80 participants in the intervention group and 40 participants in the control group. Primary outcomes focus on feasibility and use of the exoskeleton, including daily wearing time. Effectiveness-related outcomes include musculoskeletal complaints after 3 months, assessed using the Cornell Musculoskeletal Discomfort Questionnaire. Secondary outcomes include physical and mental workload (NASA-Raw Task Load Index), job satisfaction (Copenhagen Psychosocial Questionnaire), cognitive performance (Wiener Testsystem), fatigue (Fatigue Scale), acceptance of exoskeletons (Technology Commitment), user satisfaction (Quest 2.0), user experience and implementation barriers (short interviews), absences due to illness, blood pressure, physical activity (Fitbit/Garmin) and dropouts. Outcomes will be assessed at baseline, every 4 weeks during, and immediately after the intervention. The study is open-label, with blinding applied to outcome assessors and data analysts only. Primary analyses will follow the intention-to-treat principle and will be conducted using mixed-effects models with repeated measures to estimate feasibility- and effectiveness-related outcomes over time.

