## Assignment of interventions: blinding

### Who will be blinded {17a}

This study is designed as an open-label randomized controlled trial, as blinding of participants and staff delivering the intervention is not feasible due to the visible and physical nature of the exoskeleton. Consequently, neither participants nor those overseeing the intervention will be blinded. However, to mitigate potential bias, outcome assessors and data analysts will remain blinded to group assignment, and all data will be pseudonymized prior to analysis to ensure objectivity. We acknowledge the risk of performance bias and detection bias, particularly in subjective outcome measures such as perceived workload, fatigue, or job satisfaction. To address these risks, we use validated and standardized questionnaires to reduce the influence of personal interpretation. Furthermore, participants in both arms will receive comparable levels of researcher attention and contact, helping to minimize differential expectations or behavior changes that could otherwise influence the results.

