### Composition of the data monitoring committee, its role and reporting structure {21a}

No independent data monitoring committee (DMC) is established for this low-risk study. All procedures, including the development of the study protocol, the case report form, the content of participant information and consent, the application for ethics approval, data processing, central and on-site monitoring, and analyses, follow standard operating procedures (SOPs). The coordinating center is the Chair of Human-Technology Interaction, Magdeburg-Stendal University of Applied Sciences, and is responsible for data monitoring. Safety and data adequacy will be monitored every 2 weeks under the supervision of the principal investigator. During monitoring visits, the monitor will:

(1) Verify the informed consent forms; (2) Conduct a source data review of key data (e.g., primary and secondary endpoints, adverse events); (3) Discuss any open questions that have arisen during data management. Additional regular teleconferences and meetings will be held as needed to ensure compliance with appropriate quality standards and timelines.

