### Adverse event reporting and harms {22}

The interventions in this trial are expected to carry low risk. Potential adverse events related to the use of the passive back-support exoskeleton may include transient discomfort, pressure, friction, or skin irritation at points of force transmission (e.g., shoulders or hips), as well as musculoskeletal soreness associated with adaptation to wearing the device. Improper adjustment of the exoskeleton to individual body proportions may increase the likelihood of such events.

To minimize these risks, a lightweight and ergonomically adjustable exoskeleton model will be used that does not restrict the user’s range of motion. Participants will receive comprehensive initial training on correct adjustment and use of the exoskeleton, with regular checks by trial staff to ensure proper fit and safe use.

Adverse events (AEs) are defined as any unfavorable or unintended signs, symptoms, or injuries occurring during the study period, regardless of whether they are considered related to the intervention. This includes events potentially related to changes in work behavior during trial participation (e.g., musculoskeletal complaints, minor injuries, or falls occurring during routine work activities). Serious adverse events (SAEs) include events that result in death, life-threatening conditions, hospitalization, persistent or significant disability, or are otherwise considered medically serious.

All AEs and SAEs, whether solicited or spontaneously reported, as well as any unintended effects occurring from enrollment until the end of the trial, will be documented. Documentation will include onset, duration, severity, management, outcome, and the investigator’s assessment of relationship to exoskeleton use. Serious adverse events will be reported to the responsible ethics committee within 24 h of the research team becoming aware of the event.

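### The protocol says the comparison with usual work gives a clear assessment of device safety, but no adverse-event outcome is listed and device-only contacts leave any between-arm comparison open to ascertainment bias.

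*Protocol article*

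**What the plan says.** **The claim.** The protocol article, under Explanation for the choice of comparators {6b}, says: "This comparison allows for a clear assessment of the effectiveness, usability, and safety of the device relative to the current occupational norms".

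**The outcomes.** The abstract's list of secondary outcomes closes with "user experience and implementation barriers (short interviews), absences due to illness, blood pressure, physical activity (Fitbit/Garmin) and dropouts". Neither it, the Objectives {7}, Table 2, Table 3 nor the co-primary and secondary endpoints under Outcomes {12} names AEs or safety.

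**The collection of AEs.** Adverse event reporting and harms {22} defines an AE as "any unfavorable or unintended signs, symptoms, or injuries occurring during the study period, regardless of whether they are considered related to the intervention" and gives musculoskeletal complaints as one example. Its sentence on collection opens with "All AEs and SAEs, whether solicited or spontaneously reported, as well as any unintended effects occurring from enrollment until the end of the trial, will"; a written record is required for each, covering onset, duration, severity, management, outcome and relationship to the device.

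**Contact.** Who will be blinded {17a} states that "participants in both arms will receive comparable levels of researcher attention and contact". Intervention description {11a} and Participant timeline {13} say that data-collection visits are the same in both groups. Yet {11a} makes follow-up appointments and a daily wearing log part of the intervention, Table 3 marks exoskeleton training at baseline and at the week-1 call, and {22} promises recurring fit checks by trial staff.

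**The control group after month 3.** Controls then receive the device for 3 months. Trial design {8} leaves that period out of the statistical analysis; {22} does not mention it.

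**The concern.** A claim to assess safety clearly against usual work needs a between-arm comparison of harms: a defined outcome, the same ascertainment in each arm, a common window and usable precision. The article states the claim, but its outcome lists do not carry it.

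Ascertainment matters most. Spontaneous reports depend partly on how often someone has the occasion to make one. The harms that {22} anticipates (pressure, friction, skin irritation, soreness) are those that a fit check or a device appointment would bring up. Controls have no such occasion in the first 3 months. If AEs surface there, the arms differ in opportunity to report as well as in harm.

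Two features of {22} add to this. The AE definition does not require an event to be new or worse than at baseline, in a workforce chosen for heavy manual handling, and musculoskeletal complaints are also the effectiveness endpoint. And the recording window reaches into the period when controls wear the device.

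At stake is whether a reader can take an AE difference, or its absence, as evidence about the device.

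**Working it through.** **1. The plan's own numbers.** Sample size {14} seeks 80 + 40 = 120 complete datasets at up to 50% dropout: 120/(1 − 0.5) = 240, that is 80/0.5 = 160 and 40/0.5 = 80. The stated maximum of 240 is reproduced and not disputed. Since AEs are documented from enrollment, the groups available for an AE comparison lie between 80 vs 40 and 160 vs 80.

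**2. Precision.** The document gives no expected AE rate, so equal true risk p of 10% to 30% is assumed. Half-width = 1.96 × √[p(1 − p)(1/n₁ + 1/n₀)].

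| p | 80 vs 40 | 160 vs 80 |
|---|---|---|
| 10% | 1.96 × √(0.09 × 0.0375) = 11.4 points | 1.96 × √(0.09 × 0.01875) = 8.1 points |
| 20% | 1.96 × √(0.16 × 0.0375) = 15.2 points | 1.96 × √(0.16 × 0.01875) = 10.7 points |
| 30% | 1.96 × √(0.21 × 0.0375) = 17.4 points | 1.96 × √(0.21 × 0.01875) = 12.3 points |

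For an event type that is never seen, the one-sided 95% upper limit is 1 − 0.05^(1/n): 3.7% for n = 80 and 7.2% for n = 40.

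**3. Contact, side by side.**

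| Stated as equal | Tied to the device |
|---|---|
| Data-collection visits ({11a}, {13}) | Follow-up appointments described as part of the intervention ({11a}) |
| Researcher attention and contact ({17a}) | Daily wearing log for 3 months ({11a}) |
| | Exoskeleton training at baseline and the week-1 call (Table 3, not split by arm) |
| | Fit checks by staff, frequency not given ({22}) |

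Identical data-collection visits do not equalise the right-hand column. Only the general statement in {17a} would, and the text does not say how.

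**4. What unequal capture would do.** Observed risk = true risk × probability that an event is captured. The capture rates here are assumptions; none comes from the document. With equal true risk and 90% capture in the exoskeleton arms, the spurious difference is p × (0.90 − control capture):

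| True risk | Control 90% | 80% | 70% | 50% |
|---|---|---|---|---|
| 10% | 0 | 1 | 2 | 4 points |
| 20% | 0 | 2 | 4 | 8 points |
| 30% | 0 | 3 | 6 | 12 points |
| Risk ratio | 1.00 | 1.125 | 1.29 | 1.80 |

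The last cell is 0.30 × 0.90 = 27% against 0.30 × 0.50 = 15%, the extreme of this range. In the middle (20% risk, 90% vs 70%) the 4-point difference would reach nominal significance in about 7% of trials with 80 vs 40 and 11% with 160 vs 80. At the extreme the figures are about 30% and 55%.

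**5. Window.** If control AEs were counted over both 3-month periods, 3 of 6 months, or half of their observation, would be time with the device.

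**The case against.** The strongest reply is that this is a condensed article about a trial it calls low-risk, and that it does provide for harms. AEs are defined regardless of relatedness, are said to be solicited as well as spontaneous, and are recorded in detail. They also fall under monitoring: "Conduct a source data review of key data (e.g., primary and secondary endpoints, adverse events". The sentence in {6b} justifies a comparator; it is neither an objective nor a powered claim. Sick days, heart rate, blood pressure and dropouts are collected too, and discontinuations for discomfort count as study outcomes.

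Much of this stands, and it rules out several stronger readings.

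- **That nobody asks about AEs.** Table 3 has no AE row, but the query form may sit in the full protocol mentioned in {31c}. Its absence here is no error.
- **That the comparison is biased.** No section says that AEs are collected at fit checks, at the week-1 call or through device questionnaires. With equal capture the bias is zero, and the direction is not fixed either. The text supports a risk, not a result.
- **That pre-existing pain must be counted as an AE.** Onset is recorded, and medical history and the D-CMDQ are taken at baseline, so old complaints can be told apart. The definition just does not require it.
- **That safety review outruns data collection.** "Safety and data adequacy will be monitored every 2 weeks under the supervision of the principal investigator" describes central oversight, not a participant visit, and a review interval shorter than the visit interval is no defect.
- **That later control events will enter the comparison.** The exclusion in {8} may be meant to cover AEs; {22} leaves this open.

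The reply does not remove the mismatch between the claim and the listed outcomes, or between the contact asserted in {17a} and the device contacts. The other measures are not presented as safety outcomes, and the D-CMDQ is the effectiveness endpoint.

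**Conclusion.** The point holds in limited form. The article claims more about safety than its listed outcomes can deliver, and its statement of comparable contact is not reconciled with the device contacts it describes. Any between-arm AE comparison is open to ascertainment bias of unknown size and direction; the 0 to 12 points shown above only illustrate assumed capture rates. The recording window needs an explicit limit for the comparison.

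Imprecision alone makes the word clear too strong: 11 to 17 points either way with 80 vs 40 and 8 to 12 points with 160 vs 80. This rests on an assumed equal AE risk of 10% to 30% and the Wald approximation. The randomization and the effectiveness analysis are not affected.

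**What to change.** 1. Reword {6b} so that safety is described and estimated, with no promise of a clear assessment.
2. Reconcile {17a} with {11a}, Table 3 and {22}: state which contacts only device users have, and limit the statement of comparability to the data-collection visits if that is what is meant.
3. List AEs in the first 3 months as a secondary outcome, with a row in Table 3. Put one identical short query into the existing LimeSurvey questionnaires for all arms at t0, t1, t2 and t3, with a checklist of the events named in {22}. Count events that are new or worse than at t0.
4. Report the proportion with at least one solicited AE by randomized arm, with 95% confidence intervals. Show spontaneous reports, reports arising at device contacts, and events in the control group's later wearing period separately, outside the between-arm comparison.

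The cost is a slightly longer survey, one descriptive table and a more modest safety claim. Recruitment began in January 2026 and is expected to run to June 2027, so an amendment under {25} can still cover later participants. Those already past baseline will have no t0 answer, and their events would have to be classified by recorded onset.

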### Intervention description {11a}

Participants allocated to the intervention condition receive one of two passive back-support exoskeleton models (Model A or Model B) for 3 months, assigned randomly. This is accompanied by regular follow-up appointments and asynchronous educational materials on its use. This includes monitoring daily wearing time and frequency of use per week. Participants are instructed to wear the exoskeleton “as frequently as possible” during their daily work activities over the 3-month period. This instruction was deliberately chosen to obtain a realistic and practice-oriented representation of actual usage behavior in everyday work. Since occupational activities typically encompass a broad range of tasks (e.g., sitting, standing, lifting), participants are instructed to use the exoskeleton during at least 75% of all lifting tasks (see also primary applicability endpoint). No additional strategies to promote or enforce adherence are implemented, as justified non-use in this context provides important insights and represents a relevant aspect of ecological validity.

Daily wearing time will be assessed using a combination of self-reported wearing logs and objective sensor-based data. Participants will complete a daily wearing protocol documenting the duration and frequency of exoskeleton use during their work shifts throughout the 3-month intervention period.

In addition, the exoskeleton is equipped with an integrated motion sensor that records movement patterns indicative of exoskeleton use. Sensor-based measurements will be conducted during predefined measurement periods (selected full working weeks) rather than continuously throughout the entire intervention period. These data will be used to complement and validate self-reported wearing time and to assess the consistency and plausibility of self-reported usage patterns.

The control group will not receive an exoskeleton and will continue with their usual work. Participants in the control group will be instructed to continue their usual work practices and to refrain from using back braces or other back-support devices during the 3-month study period, unless medically indicated. Any medically necessary treatment or therapeutic measure may be initiated or continued at any time and will be documented.

During the intervention period, several assessments will be conducted at 4-week intervals. These assessments will include questionnaires and brief interviews to identify entry barriers, acceptance, and potential barriers to implementing exoskeletons in daily work routines, as well as to assess musculoskeletal complaints, fatigue, job satisfaction, and cognitive performance. A detailed list of the constructs to be assessed and their corresponding measurement methods is provided in Table 2. The study visits for data collection are identical in both groups.

**Table 2 Tab2:** Outcomes and operationalization

Outcomes	Data collection, operationalization
*Outcome evaluation*	
• Musculoskeletal complaints	• Cornell Musculoskeletal Discomfort Questionnaire, German version (D-CMDQ) [31]
• Sick days • Medical costs (estimate)	• Number of total sick days • Number of musculoskeletal-related sick days • Medical costs per musculoskeletal-related sick day
• Physical and mental workload • Work-related exhaustion • Job satisfaction	• NASA-Raw Task Load Index, German version (NASA-RTLX) [32] • Fatigue Scale (FS) [33] • Copenhagen Psychosocial Questionnaire, German version (COPSOQ) [34] • Resting heart rate (blood pressure monitor, Boso medicus) • Resting blood pressure (blood pressure monitor, Boso medicus)
• Attention and memory performance due to low physical exhaustion (subgroup, nursing)	• Vienna Test System (WTS) [35]
*Process evaluation*	
• Applicability of the exoskeletons in real-world work settings	• Wearing time of the exoskeleton in relation to the total time of daily physical activity
• Utilization of the exoskeletons • Acceptance among participants and employers • User satisfaction • User experience and implementation barriers	• Frequency and duration of wearing per week • Technology readiness short scale (TB) [36] • Quebec User Evaluation of Satisfaction with Assistive Technology 2.0 (QUEST 2.0) [37] • Brief interview

After the intervention, the control group will also be allowed to use the exoskeleton for 3 months (waiting-control design). However, this usage period will not be included in the statistical analysis.

A crossover design was deliberately not chosen due to important methodological and practical limitations in this occupational setting. Although laboratory studies suggest that exoskeleton use can acutely influence movement patterns, muscle activation, and perceived workload, evidence regarding the persistence and reversibility of such changes under real-world working conditions is currently limited. In particular, no evidence-based washout period can be defined. Consequently, potential carryover effects cannot be reliably excluded. To minimize the risk of residual behavioral or motor adaptations compromising internal validity, a parallel-group design was considered the more appropriate and methodologically robust approach to address the research question.

